#### Safety considerations and adverse events

Adverse events occurring during and between treatments will be recorded and compared between groups (without statistical comparisons). Training and all measurements are non-invasive and place the subject at no risk other than those that normally may occur during functional upper limb activities. Nevertheless, the patient will be free to withdraw from the study at any time. The investigator has the right to withdraw a patient from the study due to any reason concerning the health or well-being of the patient, or in case of lack of cooperation. The reason for any withdrawal will be noted in the patient’s hospital file.

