### Methodology and work plan

Approval will be obtained from each Institutional Review Board Committee (IRB) prior to commencement. All participants will sign an informed consent form and will be randomly assigned to one of the two intervention groups:
Telerehab VR trainingConventional therapy

A block randomization procedure will be performed by the study coordinator who will place numbered tickets in sealed opaque envelopes. The sealed envelopes will be opened sequentially by the investigator only after the participant’s name and other details will be written on the appropriate envelope. The participants will be informed as to the resulting group allocation before the pre-intervention tests. The assessor will then assign the participants to an intervention program. The two interventions will be comparable in length (8 weeks), frequency (twice weekly), and session duration (50–60 min). The 8-week intervention period is in accordance with other studies investigating upper limb physical rehabilitation in PwMS [2].

Pre-intervention tests (T0) characterizing groups and obtaining baseline values of primary and secondary outcome measures will be performed 1 week ± 3 days prior to the intervention program. Within 1 week ± 3 days after completion of the intervention, post-intervention tests will be performed (T1). The same tests will be conducted at a 1 month±3 days follow-up, (T2) after completion of the intervention. During the follow-up period (T1-T2), patients will be instructed to continue their regular activities. All assessments and interventions will be performed at the two MS centers. Due to the nature of the intervention, therapists and participants will not be blinded to the group allocation; however, the assessor will be blinded. Figure 2 illustrates the procedures that participants will undergo at T0, T1, and T2.

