### Outcomes

#### Primary outcomes (collected at T0, T1, T2)

##### NHPT

The NHPT was selected based on the widespread adoption and extensive data available. Furthermore, the NHPT is recommended as a gold standard for measuring manual dexterity in PwMS [32]. The NHPT has excellent psychometric properties as to reliability, discriminant, concurrent, and ecological validity; can detect progression over time; is sensitive to treatment; and, as such, is recommended for inclusion in clinical trials. Briefly explained, the NHPT requires participants to repeatedly place nine pegs into nine holes, one at a time, as quickly as possible and then remove them from the holes. The total time needed to complete the task is then recorded. Two consecutive trials with the dominant hand are immediately followed by two consecutive trials with the non-dominant hand [4, 8].

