### Statistical analysis

Data analysis will be performed by the SPSS 25.0 program. The data will be initially examined for normality violations, outliers, errors, and patterns of missing values; missing data will be replaced by multiple imputation techniques found in the SPSS. In the event of exacerbations, the analysis will be conducted with and without the individuals who had relapsed in order to identify any untoward effects on the outcomes. The data analysis itself will follow intent-to-treat principles. The effect of the intervention on the NHPT (aim 1), ARAT (aim 1), MAM-36 (aim 1), SF-36 (aim 2), and adherence and user satisfaction (aim 3) will be examined using the Condition × Time mixed model multivariate analysis of variance (MANOVA) followed by an inspection of the univariate F-ratios. Conditions will be a between-subjects factor and time and a within-subjects factor. Interactions and main effects will be further calculated using post hoc analyses with a correction of alpha. Effect sizes associated with univariate *F*-statistics will be expressed as eta-squared (*η*^2^), and effect sizes based on a difference in mean scores will be expressed as Cohen’s *d*. We will include cognitive scores (BRB-N) as covariates in all final statistical analyses.

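### The stated adverse event window does not reach T1 or T2, although T2 is an outcome visit and relapses up to T2 bear on the planned analysis with and without relapsed participants

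*Protocol article*

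**What the plan says.** **Safety window.** The section Safety considerations and adverse events contains the only recording rule for adverse events in the article: "Adverse events occurring during and between treatments will be recorded and compared between groups (without statistical comparisons". It adds that the reason for any withdrawal goes into the patient's hospital file.

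**Schedule.** Methodology and work plan fixes the treatment period: "The two interventions will be comparable in length (8 weeks), frequency (twice weekly), and session duration (50–60 min". The first outcome visit comes after that: "Within 1 week ± 3 days after completion of the intervention, post-intervention tests will be performed (T1". The second comes later still: "The same tests will be conducted at a 1 month±3 days follow-up, (T2) after completion of the intervention". No study treatment is given between these visits: "During the follow-up period (T1-T2), patients will be instructed to continue their regular activities".

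**Use of T2.** The Outcomes section heads the nine-hole peg test with "Primary outcomes (collected at T0, T1, T2". The main hypothesis at the end of the Background covers both the end of the intervention and the one-month follow-up. The Statistical analysis section makes time a within-subjects factor.

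**Relapses.** The same section states: "In the event of exacerbations, the analysis will be conducted with and without the individuals who had relapsed". It does not limit this to relapses during training, and it does not say where relapse data come from.

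**The concern.** The safety rule and the analysis cover different periods. The rule covers sessions and the gaps between them. The analysis runs to T2, a month after there are any sessions to fall between.

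Two things are at stake.

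- **The safety comparison.** The Discussion asks whether patients can exercise safely at home. Earlier experience with the platform was five patients asked to do one 30-minute session each, and there is no data monitoring committee. The descriptive comparison of adverse events between arms is the only safety comparison described. An event that appears after the last session, such as delayed overuse pain, falls outside it as worded.
- **The relapse set.** The comparison with and without relapsed participants is informative at T2 only if relapses up to T2 are known. The exclusion criteria already treat a relapse in the 90 days before enrolment as disqualifying. A relapse in the month before T2 is well inside that span, and if unrecognised it could be read as fading of the training effect.

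**Working it through.** The article states no figure on this point to reproduce. The check sets the texts side by side and then sizes the gap.

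**Step 1: does any text extend the window?** The safety section gives sessions and the time between them. Methodology and work plan puts T1 and T2 after the intervention is complete and describes the time from T1 to T2 as regular activities. No other section adds a later end point for adverse events. The stated window therefore stops before two of the three assessments.

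**Step 2: does the analysis need information from after the window?** T2 is in the hypothesis, in the primary outcome schedule and in the time factor. The relapse analysis carries no time limit. So it does.

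**Step 3: is relapse capture tied to the adverse event record?** No sentence ties them, and no sentence names any other source. The source of relapse data is open.

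**Step 4: length of the gap.** Inputs: treatment 8 weeks × 7 = 56 days; T2 at one month ± 3 days after completion. The article does not give one month in days, so 28 to 31 days is an assumption, with 30 as the centre. The last session is taken to fall at the end of the 8 weeks.

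Share outside the window = days to T2 / (56 + days to T2)

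| Case | Days to T2 | Share |
|---|---|---|
| Shortest (28 − 3) | 25 | 25/81 = 31% |
| Centre | 30 | 30/86 = 35% |
| Longest (31 + 3) | 34 | 34/90 = 38% |

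**Step 5: how many relapses might fall there?** The documents give no relapse rate, so annual rates are assumed. Expected number among 24 participants = 24 × rate × 30/365; chance of at least one = 1 − exp(−expected), under a Poisson model.

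| Assumed annual rate | Expected in 30 days | Chance of at least one |
|---|---|---|
| 0.1 | 0.20 | 18% |
| 0.2 | 0.39 | 33% |
| 0.3 | 0.59 | 45% |
| 0.5 | 0.99 | 63% |
| 1.0 | 1.97 | 86% |

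These are relapses that could occur in the period, not relapses that would go unrecorded. One participant is 1/12 = 8.3% of an arm.

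**The case against.** The strongest reply is that the article gives no explicit end date for safety recording and does not exclude later events. It condenses a full protocol (version 2.0), which may set the safety follow-up and the source of relapse data. The figures showing the study schedule and the visit procedures cannot be seen here. Participants come from two MS centres and return to them at T1 and T2, so relapses could be identified at those visits without any adverse event form. Relapse also appears as an item of its own in the exclusion criteria. Finally, the training is described as non-invasive, with no risk beyond ordinary upper limb activity.

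Much of this stands, and it rules out three stronger readings that a reader might infer:

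- **That about a third of on-study relapses will go unrecorded.** The 35% is a share of calendar time. It becomes a share of missed relapses only if the adverse event record is the sole source, which the article does not say.
- **That the analysis without relapsed participants will wrongly keep people who relapsed late.** It could, if no other route exists. The article does not show that none exists.
- **That events in people who stop training early are lost.** The article does not say that their observation ends, and reasons for withdrawal have a stated place of record.

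What the reply does not remove is the sentence itself. The article is not silent on the window; it states one, and the one stated stops short of T1 and T2. If the full protocol goes further, the published sentence misdescribes it and still needs correcting.

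**Conclusion.** The point holds as a mismatch between a stated rule and the trial's own schedule. The adverse event window, as worded, leaves out roughly 30 of the 86 days from first session to T2 (31% to 38%), while T2 is an outcome time point and the relapse analysis has neither a time limit nor a named data source. Followed literally, the rule would drop late adverse events from the comparison between arms. Relapses between the last session and T2 could be missed, but only if nothing else captures them.

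This rests on the plain reading of the window and on taking one month as 28 to 31 days. The relapse counts rest on assumed rates and show scale only. Severity is minor: no sample size, test or primary estimate depends on it. It is still worth changing, because the trial had not begun when the article was written and events that nobody asks about at the time may not be recoverable later.

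**What to change.** Replace the recording sentence in Safety considerations and adverse events with wording to this effect: *Adverse events and MS relapses will be recorded from randomisation to T2 for every randomised participant, whether or not training was completed, with a direct question at T1 and T2. They will be tabulated by arm, separately for the training period and the follow-up period, without statistical tests.*

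In Statistical analysis, add that the participants counted as relapsed are those with a relapse in this record up to T2. If the full protocol already names another source of relapse data, cite that source there instead.

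The cost is one question at two visits that already take place and slightly more data entry. No visit, treatment or sample size changes.

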### Outcomes

#### Primary outcomes (collected at T0, T1, T2)

##### NHPT

The NHPT was selected based on the widespread adoption and extensive data available. Furthermore, the NHPT is recommended as a gold standard for measuring manual dexterity in PwMS [32]. The NHPT has excellent psychometric properties as to reliability, discriminant, concurrent, and ecological validity; can detect progression over time; is sensitive to treatment; and, as such, is recommended for inclusion in clinical trials. Briefly explained, the NHPT requires participants to repeatedly place nine pegs into nine holes, one at a time, as quickly as possible and then remove them from the holes. The total time needed to complete the task is then recorded. Two consecutive trials with the dominant hand are immediately followed by two consecutive trials with the non-dominant hand [4, 8].

#### Secondary outcomes (collected at T0, T1, T2)

##### Action Research Arm Test (ARAT)

The ARAT is a 19-item observational measure used by physical therapists and healthcare professionals to assess upper extremity performance in terms of coordination, dexterity, and functioning in several neurologic conditions, including MS [36]. Items comprising the ARAT are categorized into four subscales (grasp, grip, pinch, and gross movement) and arranged in order of decreasing difficulty, with the most difficult task examined first, followed by the least difficult task. Task performance is rated on a 4-point scale, ranging from 0 (no movement) to 3 (movement performed normally).

##### Manual Ability Measure-36 (MAM-36)

The MAM-36 is a questionnaire based on perceived ease or difficulty that a person may experience when performing unilateral and bilateral ADL tasks. During a semi-structured interview, the subject is asked to rate 36 unilateral and bilateral ADL tasks using a 4-point scale. The scores of the different tasks are summed up and transformed using a Rasch-derived conversion table. The MAM-36 has adequate psychometric properties and is recommended as an outcome measure for upper limb function in PwMS [37].

##### Health status questionnaire (SF-36)

The Short Form-36 is one of the most widely used generic measures of health-related quality of life and has been shown to discriminate between subjects with different chronic conditions and between subjects with different severity levels of the same disease. The instrument addresses health concepts relevant to MS patients from the patient’s perspective. Availability of normative data makes the SF-36 beneficial for comparative purposes. There is considerable evidence of the validity of the SF-36 in PwMS [38].

##### Adherence and user satisfaction

Adherence to exercise will be evaluated at the end of the intervention phase by examining the patient’s exercise diaries. The User Satisfaction Evaluation Questionnaire (USEQ) will be used to assess the participants’ satisfaction with the training program [39]. The USEQ is a reliable questionnaire with internal consistency designed to evaluate the satisfaction of the user in virtual rehabilitation systems.

##### Impression of change (collected only at post-intervention T1)

A 7-point Likert-type global rating scale from both the patient and therapist’s perspective will be applied. The question that will be asked will be “Compared to before treatment, at present, how would you rate your/the participant’s functional upper limb activities?” The responses will be rated as 1 = worse than ever, 2 = much worse, 3 = slightly worse, 4 = unchanged, 5 = slightly improved, 6 = much improved, and 7 = greatly improved.

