#### Telerehab VR intervention

The telerehab VR intervention consists of a custom-made software program, that will run on a personal computer (or tablet), developed under Unity (Unity Technologies Inc., San Francisco, USA). Unity is a cross-platform game engine worldwide adopted to create three-dimensional, two-dimensional, virtual reality, and augmented reality games, as well as simulations and other experiences. PwMS will be requested to perform several ADLs from the three main areas of self-care, dressing, and meal preparation. Taking place in a realistic home scenario, the PwMS will pick up objects and move them to a predefined target clearly indicated on the screen. Hand and object trajectory are controlled by a low-cost non-contact infrared controller (Leap Motion). This instrument was proven successful in upper limb rehabilitation of individuals with neurologic and orthopedic conditions [33–35].

During the exercise, the hand coordinates will be continuously recorded; thus, data kinematic data calculated on the basis of the 3D trajectory like speed, accuracy on target placement, and movement smoothness will be accessible. This data will be stored in the PC/tablet and will also be sent remotely to the clinical center for further analysis/processing. Both target position and task complexity will define the exercise difficulty, which can be modified (i.e., increased or decreased) automatically on the basis of the previous performance or manually modified by the user. A suitable period of familiarization with the installation/management of the hardware and software will be carried out under the supervision of engineers and therapists to ensure that the exercises are being correctly performed. A schematic representation of the system is shown in Fig. 3.

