#### Conventional therapy

Conventional therapy will focus on task-related upper-limb treatments while in sitting denoting the standard care for PwMS [2]. Several manual techniques, therapy tools and objects of ADL will be allowed during treatment. Use of additional electrical or mechanical therapy devices (i.e., support arm systems, splints) will be avoided. The interventions will be conducted on a one-on-one basis in the physiotherapy or occupational therapy department of each participating center. Training and therapy content will be tailored to each participant’s preferences, the agreed movement aims and their motor function level.

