## Discussion

The TEAMS project has tremendous potential to improve the quality of evidence and informed decisions of functional upper limb activities in PwMS. The project addresses the needs of PwMS [2, 6, 8], specifically, if they are provided access to functional upper limb exercises and does the location where the exercises are performed impact their outcomes? Is it necessary to travel to a healthcare facility with access to equipment and MS experts in order to benefit from upper limb exercises or can the PwMS safely and effectively exercise in their own home, if provided with expert guidance? We will compare a conventional healthcare facility training program with a VR telerehab home-based program. This information will impact the PwMS’s informed decisions as to how to spend their time and potentially limited resources.

If comparable results are found between the treatments in improving upper limb outcomes, this would suggest that PwMS can choose the program that best meets their personal needs, e.g., financial concerns, transportation, or accessibility issues. Secondly, this information can be used by healthcare providers and medical professionals by developing upper limb exercise programs that will most likely succeed and can then be distributed to neurologists and other medical providers. Finally, increasing an individuals’ accessibility to upper limb exercise options may prevent or slow the decline of disability, increase independence in ADL functions, and help maintain a better quality of life.

The telerehab VR proposal for restoring upper limb functional activities in PwMS is an expansion of a project originally developed by the University of Cagliari (Italy) that included a feasibility study which produced encouraging results. The following goals were reached during the initial phase: (1) recruitment of technological developers and MS professionals, (2) definition of upper limb functional difficulties and relevant rehabilitation exercises of the population target, and (3) development of a hardware-software VR platform based on low-cost tools, encouraging self-practice of functional exercises of the upper limb. Important elements include a user-friendly system that can be easily assembled, used in the home and be monitored from a distance by a medical/rehab professional.

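### The only observer-side impression-of-change rating comes from an unblinded therapist who appears to have unequal opportunity to observe the two arms

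*Protocol article*

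**What the plan says.** Under Impression of change, listed among the secondary outcomes and collected at T1 only, the protocol article states: "A 7-point Likert-type global rating scale from both the patient and therapist’s perspective will be applied". The question asks how upper limb function now compares with before treatment, answered from 1 (worst) to 7 (best). No third rater is named.

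On blinding, Methodology and work plan says "therapists and participants will not be blinded to the group allocation; however, the assessor will be blinded".

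On contact between therapist and participant:

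- Conventional therapy: "The interventions will be conducted on a one-on-one basis in the physiotherapy or occupational therapy department of each participating center". The abstract gives 16 sessions per group.
- Telerehab VR intervention: familiarization "will be carried out under the supervision of engineers and therapists to ensure that the exercises are being correctly performed", and movement data that "will also be sent remotely to the clinical center for further analysis/processing".
- Discussion: the system is meant to be "used in the home and be monitored from a distance by a medical/rehab professional".
- Methodology and work plan, in contrast: "All assessments and interventions will be performed at the two MS centers".

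**The concern.** A participant's own rating cannot be blinded in this design. An observer's rating can be, because a blinded assessor is already planned for T0 and T1. The plan instead takes the observer-side view from a therapist who knows the allocation.

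Unequal observation compounds this. A rater who has worked with someone over many sessions is better placed to judge change since before treatment than one who saw that person during familiarization and afterwards mainly through remote data. Where direct knowledge is thin, ratings may drift towards no change or towards what the rater expects. The bias could therefore run in either direction and could create a difference between arms or hide one.

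That matters because the main hypothesis is of no difference between programs, and the Discussion says that comparable results would let patients choose either one. If the therapist's rating were used to support or undermine comparability, its result could not be separated from knowledge of allocation and amount of contact.

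**Working it through.** The point concerns design, and the plan gives no figure for this outcome to reproduce. The check is a comparison of sections, followed by an illustration of scale.

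**Comparison of sections**

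1. Who rates: patient and therapist (Impression of change).
2. Who is blinded: the assessor only (Methodology and work plan). Both raters of this item are therefore unblinded.
3. Contact in the conventional arm: one-on-one in the department, twice weekly for 8 weeks, so 2 × 8 = 16 sessions, which agrees with the abstract.
4. Contact in the VR arm: a familiarization period of unstated length, then home use with data sent to the center and monitoring from a distance. No other in-person contact with a therapist is described.
5. Conflict: one sentence in Methodology and work plan places every intervention at the centers, while the abstract, the aims and the Discussion describe a home-based program. Read literally, that sentence would remove much of the difference between items 3 and 4. The unequal observation is therefore implied by most of the text but not stated consistently.
6. Use in the analysis: Statistical analysis names the nine-hole peg test, ARAT, MAM-36, SF-36, adherence and satisfaction. It does not name impression of change.

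**Illustration of scale**

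Inputs: 12 per arm (Sample size section). Assumed, because the documents give nothing: SD of 0.8 to 1.2 points, differential bias b of 0.25, 0.5 or 1 point, no true difference, two-sided 5% test, normal approximation.

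Standard error of a difference in means: SE = SD × √(2/12) = 0.408 × SD. At SD 1 this is 0.41 points.

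Probability of a significant result: P = 1 − Φ(1.96 − b/SE) + Φ(−1.96 − b/SE).

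For b = 0.5 and SD = 1: b/SE = 0.5/0.408 = 1.22, and P = 0.232.

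| Bias (points) | SD 0.8 | SD 1.0 | SD 1.2 |
|---|---|---|---|
| 0.25 | 0.119 | 0.094 | 0.080 |
| 0.5 | 0.334 | 0.232 | 0.175 |
| 1.0 | 0.865 | 0.688 | 0.532 |

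A bias of 0.25 points is below one standard error at SD 1, and a bias of 0.5 points is above it. The table shows what a given bias would do. It is not evidence that a bias of any particular size will occur, and the normal approximation is rough for a 7-point scale with 12 per arm.

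**The case against.** A reader might infer that the two arms are scored by different, interested therapists. The documents do not support that. The Interventions section describes one pool of physiotherapists and occupational therapists for both programs, and nothing says that different people serve each arm. That the rater is the participant's own treating therapist is the natural reading but is not stated. That VR participants are seen mainly remotely is an inference, and the sentence placing all interventions at the centers contradicts it. An allegiance to one program is nowhere documented.

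A reader might also infer that the rating will be presented as an independent clinical judgement of comparability. The article does not say so. It calls the rating a perspective, neither hypothesis names it, and it is absent from the analysis section. Its place under the secondary outcomes carries limited weight, since the baseline-only cognitive battery is listed there too.

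Two further objections concern the remedy. First, the same section that calls the assessor blinded also has the assessor assign participants to a program, so moving the question does not by itself secure a blinded rating. Second, an assessor who sees only the test sessions may largely restate the nine-hole peg test and ARAT, whereas the therapist's view may be wanted as a complement to them.

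These objections narrow the point but do not remove it. Even if the same therapists rate both arms, they are unblinded and, on most of the text, see the arms unequally. Nor is this a detail left to a fuller document: the article names the rater, and an analysis plan cannot blind a rating after it has been collected. The conflict over the assessor is a condition on the fix.

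**Conclusion.** The concern holds in limited form. It is documented that the only observer-side rating of change comes from an unblinded therapist although a blinded assessor is planned. Unequal opportunity to observe the arms is implied by the description of the two programs, subject to the conflicting statement on location. A between-arm reading of this item is therefore open to differential rating bias of unknown direction and size. The 18 to 33% false-positive range for a half-point bias rests wholly on assumed inputs.

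The reach is small: one subjective secondary item, not named in the stated analysis. The nine-hole peg test is not affected by this point. The change is still worth making because it is cheap and can only be made before the ratings are collected.

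**What to change.** 1. Reconcile the two statements about the assessor in Methodology and work plan. Give assignment to programs to someone else, so that the person who tests participants does not learn the allocation that way.
2. Have that assessor answer the same 7-point question at T1 for every participant in both arms, from the T0 and T1 examinations. Use this as the observer-side rating in any between-arm comparison. The same person should see a given participant on both occasions.
3. Keep the therapist's rating, if wanted, as a descriptive item labelled unblinded and reported within arm only. The patient's rating stays as it is and is also labelled unblinded.
4. Reconcile the sentence placing all assessments and interventions at the centers with the home-based description of the VR arm.

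The cost is one extra question on an existing form and a change in who handles assignment, with no additional visit. The downside is that the assessor's view rests on two test sessions and may overlap with the nine-hole peg test and ARAT. Participants know their arm and could reveal it at T1, so some risk of unblinding remains. The article describes the trial as not yet begun, so on its own account the change could precede data collection.
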